### Outcome measures

#### **
*Primary outcomes*
**

The primary outcome will be the delivery of selected health care practices to women attending the first antenatal care visit. Three practices will be chosen from the list of priority practices below, after evaluating their current use during the baseline period and before implementation of the intervention. Practices that are not selected as primary outcomes will be incorporated as secondary outcomes.

• Frequency of women receiving screening for syphilis

• Frequency of women receiving screening for HIV

• Frequency of women receiving screening for anaemia

• Frequency of women receiving screening for hypertension

• Frequency of women receiving tetanus toxoid

• Frequency of women receiving intermittent preventive malaria treatment

• Frequency of women receiving iron supplementation

• Frequency of women receiving anti-parasitic treatment (de-worming)

• Frequency of syphilis sero-positive women receiving the administration of syphilis treatment

• Frequency of HIV sero-positive women receiving administration of antiretroviral treatment.

#### **
*Secondary outcomes*
**

Selected practices in each ANC visit after the first ANC visit:

• Frequency of women receiving screening for syphilis

• Frequency of women receiving screening for HIV

• Frequency of women receiving screening for anaemia

• Frequency of women receiving screening for hypertension

• Frequency of women receiving tetanus toxoid

• Frequency of women receiving intermittent preventive malaria treatment

• Frequency of women receiving iron supplementation

• Frequency of women receiving anti-parasitic treatment (de-worming)

• Frequency of syphilis sero-positive women receiving the administration of syphilis treatment

• Frequency of HIV sero-positive women receiving administration of antiretroviral treatment

• Frequency of midwives’ positives attitudes and readiness to provide the selected practices.

#### **
*Composite outcome*
**

A score will be computed. One point will be added to the score for each selected practice that was implemented. A woman receiving all selected practices will get the highest possible score, while a woman who receives none of the practices will get a score equal to zero. Two sets of scores will be computed, one for the first ANC visit, and one for subsequent visits.

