### Data collection and management

#### **
*Source of data for primary outcomes*
**

The Ministry of Health of Mozambique has designed a data collection instrument to be used for the registration of ANC data at national level in order to obtain uniform and comprehensive data from all health units. This pre-printed Book of Registration of Antenatal Care Data (Livro de Registro da Consulta Pre-natal) has been distributed to all health facilities, and all ANC providers are required to complete it for each ANC visit. The unit of registration is the antenatal visit (not the woman visited). However, in order to be able to compute individual-based indicators, a system will be in place by which each woman will be assigned a code/number that will be reflected in the logbook. The visits and the women will be linked by this code maintaining, however, the anonymity of the woman. This will be achieved by means of a card (the size of a visiting card) that would be given to the mother on the first ANC visit and should be carried with her ANC card to every ANC visit. This card will be assigned a code/number and will be composed of 12–15 small stickers with the same code/number. When the woman comes to the ANC visit, the nurse will take one of the stickers and place it in the logbook in the row corresponding to that visit.

The variables in the registration book are the following: date of prenatal visit, name, age, address, number of ANC visits for this pregnancy, gestational age, blood pressure, malnutrition, anaemia, proteinuria, examination of the breast (presence of nodules), screening and treatment of syphilis (for the woman and her partner) and other sexually transmitted infections, tetanus immunization status, screening, prevention and treatment of maternal-to-child transmission of HIV, prevention of malaria with intermittent preventive treatment, iron administration, anti-parasitic treatment, distribution of bed nets, partner coming to the visit, reference to another health facility and name of health provider.

#### **
*Quality data monitoring and quality control*
**

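### Two candidate primary outcomes count only sero-positive women, a group whose membership the intervention itself changes; the additive score has a related but small flaw

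*Protocol article*

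**What the plan says.** Under Outcome measures, the protocol article fixes the primary outcome in two steps: "Three practices will be chosen from the list of priority practices below, after evaluating their current use during the baseline period". The list has ten entries. Eight are frequencies among women in general. Two have a restricted denominator: "Frequency of syphilis sero-positive women receiving the administration of syphilis treatment" and "Frequency of HIV sero-positive women receiving administration of antiretroviral treatment". The same ten reappear for later visits under the heading "Selected practices in each ANC visit after the first ANC visit".

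The composite outcome is a plain sum: "One point will be added to the score for each selected practice that was implemented". Its top value is defined by "A woman receiving all selected practices will get the highest possible score", and "Two sets of scores will be computed, one for the first ANC visit, and one for subsequent visits". No rule is given for a practice that does not apply to a woman.

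The outcome data come from the national registration book. Among its variables the article names "screening and treatment of syphilis (for the woman and her partner) and other sexually transmitted infections" and a corresponding HIV item. No separate testing of all attenders is described, and the Ethical aspects section says that no additional tool was developed to collect data on the women's health. Table 2 shows that kit A, used at the first visit, contains the rapid tests for HIV and syphilis as well as the treatments. Kit B, for follow-up visits, leaves out the syphilis test, benzathine penicillin and mebendazole.

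**The concern.** A treatment frequency among sero-positive women needs to know who is sero-positive. Here that is known only where the book holds a test result or an earlier status. Screening for both infections is itself on the outcome list and is meant to rise once the kits arrive. The denominator is therefore measured after rollout and depends on the intervention. Before rollout it holds mainly women whose status was already known, plus the few who were tested. After rollout it holds many more newly detected women. If the two groups are treated at different rates, the ratio moves even when nobody's treatment changes. Randomising the order of clinics does not protect this comparison, because the selection happens after the switch and inside each clinic.

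At stake is a primary result. If either treatment is among the three practices chosen, the trial could report no effect, or harm, on treatment while more infected women are treated.

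The score has a related weakness. It gives no point for a treatment that a woman does not need, so it depends partly on infection status as well as on care received.

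**Working it through.** The plan gives no figure on this point: it states no prevalence, treatment rate or share of women with known status. The 30% and 60% below are the frequencies assumed in the sample size section, used here as screening rates. All other inputs are assumptions.

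**1. The treatment outcomes**

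Notation: k is the share of infected women already known to be positive, q the screening rate among the rest, a the treatment rate in known positives, and b the treatment rate in newly detected positives.

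- Detected share of all infected women: D = k + (1 − k)q
- Treated share of all infected women: T = ka + (1 − k)qb
- Outcome as defined, if sero-positive means recorded as positive: T / D

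Take a = 90% and b = 50%, both unchanged by the intervention.

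| k | q | D | T | T / D |
|---|---|---|---|---|
| 20% | 30% | 0.20 + 0.80 × 0.30 = 0.44 | 0.18 + 0.12 = 0.30 | 68.2% |
| 20% | 60% | 0.20 + 0.80 × 0.60 = 0.68 | 0.18 + 0.24 = 0.42 | 61.8% |
| 40% | 30% | 0.40 + 0.60 × 0.30 = 0.58 | 0.36 + 0.09 = 0.45 | 77.6% |
| 40% | 60% | 0.40 + 0.60 × 0.60 = 0.76 | 0.36 + 0.18 = 0.54 | 71.1% |

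The ratio falls by about 6.5 points in both cases, while the treated share of all infected women rises by 12 or 9 points. No change in treatment practice was put in, so the fall comes from selection alone.

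The direction depends on the assumptions. With the two rates exchanged (a = 50%, b = 90%, k = 20%), T / D goes from (0.10 + 0.216) / 0.44 = 71.8% to (0.10 + 0.432) / 0.68 = 78.2%, an apparent gain with no change in treatment practice. If there are no known positives and everyone detected is treated at 60%, T / D stays at 60% while T doubles from 0.30 × 0.60 = 18% to 0.60 × 0.60 = 36%.

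**2. The score**

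Suppose all ten practices are scored, each is delivered at rate q, and a treatment needs both detection and delivery. The mean score is then 8q + (p_S + p_H)q², where p_S and p_H are the syphilis and HIV prevalences. The assumed range runs from 2% and 5% to 10% and 25%.

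- At q = 60%: 4.80 + 0.07 × 0.36 = 4.83, and 4.80 + 0.35 × 0.36 = 4.93. Case mix moves the mean by 0.10.
- At full delivery: 8 + 0.07 = 8.07, and 8 + 0.35 = 8.35.
- For comparison, raising delivery of the eight general practices from 30% to 60% adds 8 × 0.30 = 2.4 points.

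The case-mix effect on the mean is therefore about 0.1 point beside a rise of about 2.4.

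**3. Follow-up list against kit B**

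The follow-up practices include syphilis screening, syphilis treatment and de-worming. Table 2 describes kit B as holding everything needed for follow-up consultations, yet it omits the syphilis test, benzathine penicillin and mebendazole. The two places do not agree on what is meant to be delivered after the first visit, so the maximum of the follow-up score cannot be read from the article.

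**The case against.** Several objections carry weight.

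- The text says sero-positive; it does not say found positive by screening at this visit. Some women will be known from earlier tests. That stands, and the working allows for it. It does not remove the problem, because a mix of known and newly detected women is exactly what shifts.
- Treatment given detection is a legitimate quantity, and the screening frequencies are reported separately, so a reader could put the two together. That is fair for a descriptive measure. It does not repair a primary comparison between differently selected groups of women.
- The score is a short sketch, separate from the primary outcomes, and the handling of practices that do not apply may be set out in a fuller document. This is a good reason to treat the score as the lesser point. Stable prevalence differences between regions are also largely absorbed, since every clinic contributes both control and intervention periods to the mixed model.

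Three stronger readings are tempting but not supported. A reader might infer that the primary result is biased; that follows only if a treatment is chosen among the three, and the choice is still open. A reader might infer that every sero-negative woman with complete care scores 8 of 10. At the first visit it is unclear whether the selected practices are three or ten, and at follow-up kit B puts two of the eight general practices in doubt. Finally, an example in which treatment among detected women worsens, say from 90% to 80%, would show nothing about selection, because the outcome would only return the fall that was put in.

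**Conclusion.** The concern holds for the two treatment outcomes. As candidates for the primary set they compare groups whose membership the intervention is designed to change. Under constant treatment rates the distortion is about 6.5 percentage points in the illustrations, and it can run against a true gain of 9 to 12 points in the treated share of all infected women. The size and sign rest on assumed values for the known share and the two treatment rates. The mechanism rests on the registration book being the source of sero-status and on the kits supplying the tests, both of which the article indicates.

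The score point is secondary. The missing applicability rule deserves correction, but its effect on the mean is about 0.1 point under the assumed prevalences and is largely absorbed by clinic effects. The article does not support a claim that the score seriously confuses case mix with quality of care.

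**What to change.** 1. State that the three primary outcomes will be chosen only from the eight practices defined for all women.
2. Report each treatment as women treated per all first-visit attenders. Keep treatment among detected women as a secondary, descriptive measure, shown beside the screening rate.
3. Build each score only from practices that apply to every woman at that visit. Reconcile the follow-up practice list with the contents of kit B before fixing the follow-up score.

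Two apparent alternatives are weaker. An outcome of tested and, if positive, treated would nearly repeat the screening outcome: at an assumed 5% positivity and 60% screening, treating none of the positives gives 0.60 × 0.95 = 57%, and treating all gives 60%. A score of practices received over practices applicable needs eligibility that is unknown in unscreened women, so it brings back the same detection-dependent denominator.

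The cost is wording only. The register already lists screening and treatment, and the primary outcomes are picked after baseline, so the change can be made before that choice. The downside is that the treatments leave the score and the primary candidate list. Treated per attender is also a low-frequency outcome with less precision: at an assumed 5% prevalence, the rise from 30% to 42% of infected women treated appears as 0.05 × 0.30 = 1.5% to 0.05 × 0.42 = 2.1% of attenders.

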### Process measures

Process data will be collected during the intervention period at prenatal clinics. The objectives of this process evaluation are: 1) to detect implementation problems that could be explanatory in case the intervention was not effective; and 2) to facilitate the replication and scale-up of the intervention if it is proven effective.

### Data collection and management

#### **
*Source of data for primary outcomes*
**

The Ministry of Health of Mozambique has designed a data collection instrument to be used for the registration of ANC data at national level in order to obtain uniform and comprehensive data from all health units. This pre-printed Book of Registration of Antenatal Care Data (Livro de Registro da Consulta Pre-natal) has been distributed to all health facilities, and all ANC providers are required to complete it for each ANC visit. The unit of registration is the antenatal visit (not the woman visited). However, in order to be able to compute individual-based indicators, a system will be in place by which each woman will be assigned a code/number that will be reflected in the logbook. The visits and the women will be linked by this code maintaining, however, the anonymity of the woman. This will be achieved by means of a card (the size of a visiting card) that would be given to the mother on the first ANC visit and should be carried with her ANC card to every ANC visit. This card will be assigned a code/number and will be composed of 12–15 small stickers with the same code/number. When the woman comes to the ANC visit, the nurse will take one of the stickers and place it in the logbook in the row corresponding to that visit.

The variables in the registration book are the following: date of prenatal visit, name, age, address, number of ANC visits for this pregnancy, gestational age, blood pressure, malnutrition, anaemia, proteinuria, examination of the breast (presence of nodules), screening and treatment of syphilis (for the woman and her partner) and other sexually transmitted infections, tetanus immunization status, screening, prevention and treatment of maternal-to-child transmission of HIV, prevention of malaria with intermittent preventive treatment, iron administration, anti-parasitic treatment, distribution of bed nets, partner coming to the visit, reference to another health facility and name of health provider.

#### **
*Quality data monitoring and quality control*
**

A comprehensive quality assurance and quality control will be put in place to ensure that the best possible data will be filled in the registration book and entered into the database. Guidelines for collecting data and filling in the registration book will be produced. To ensure that the data will be collected in a standardized way in all the participating clinics, a pilot testing of data collection and data management will be conducted prior to the start of the baseline data collection. Data quality monitoring reports will be produced regularly for each clinic. Site monitoring visits to the participating clinics will be conducted routinely and source data verification (SDV) will be performed to ensure that the data collected are complete, accurate and reliable.

Additionally, data quality control mechanisms will be implemented in order to ensure reliability of the data obtained through routine data collection. These mechanisms will include surveys on a random sample of pregnant women attending ANC clinics at exit from the facilities. Selected women will be approached as they are leaving the facility after the ANC visit to conduct the exit survey and they will be asked to participate by signing a consent form. These women will be invited to answer a set of questions related to the practices and other variables collected in the registration book (primary source of data) in order to evaluate if the information registered is identical to the data collected in the exit survey. If differences are observed, providers will be interviewed in order to resolve them. Three surveys will be conducted for this purpose at three points in time; each time point with 1000 surveys (100 questionnaires per clinic). The first survey will be carried out just before starting intervention; the second at 12 months and the last at 20 months, approximately.

#### **
*Source of data for secondary outcomes: willingness of health professionals who provide antenatal care to adopt the practices recommended in the WHO model*
**

The data will be collected at two data points: one within the first four months of the study period and the second within the last two months of the study period. A self-administered questionnaire on paper forms will be used. These forms will be sent to the data management center.

This survey is designed to assess the willingness of health professionals who provide antenatal care to adopt the practices recommended. The questions are about their perceptions of these practices and viewpoints on any barriers or facilitating factors that may affect the adoption of these practices and national guidelines.

The survey will be administered in all participating health care centers. The information obtained from this questionnaire the first time will be used as baseline data and will be compared to results from the same questionnaire administered after the intervention. The project data collector will be responsible for the administration of the surveys, and informed consent will be obtained from all participants. The questionnaire will be provided to health care professionals in an unmarked opaque envelope.

#### **
*Data management*
**

A web-based data management (DM) system will be used to enter the data and to monitor the data quality. The system will be developed by the Biostatistics and Data Management (SIS) team at UNDP/UNFPA/UNICEF/WHO/World Bank Special Programme of Research, Development and Research Training in Human Reproduction (HRP) at WHO in Geneva using the OpenClinica Application available at: https://www.openclinica.com, version 3.1.3 [30]. The system will include programmed edit checks to validate completeness, accuracy and consistency of the data entered. The OpenClinica system is an open-source software, highly secure and reliable web-based solution, fully compliant with Good Clinical Practice (GCP) and regulatory guidelines as well as the HRP/WHO Standard Operating Procedures (SOPs) for managing clinical trials. These procedures have been used in previous international multicentre trials sponsored or coordinated by WHO in the past five years and proven to be efficient. The online data entry system minimizes the delays in data queries, completion of forms and problem resolution; it makes the dataset quickly available and permits continuous assessment of data quality.

Data management will be performed locally in Maputo by the Consultorio de Estatistica e Serviço de Soluçoes-LDA (CESS) and by the WHO/SIS team. The team in Maputo will be trained in data-entry and data management using the OpenClinica system.

The nurses of all participating clinics will be trained in data collection and filling the registration book following an instructions booklet. Research assistants from clinics will be trained to take digital photos of the registration book and send them to the data management center. Photos will be sent from each facility by email on weekly basis. CESS will be responsible for verifying the data from the photos, uploading them to *dropbox* and entering the data into the OpenClinica system. Double data entry will be performed to minimize errors. Queries on data (missing values, outliers, inconsistencies and other errors) will be generated automatically in the system. Data quality will be monitored online by the WHO/SIS Team at WHO.

Standard ASCII or SPSS or SAS datasets will be generated from the final study database ready for analysis.

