### Study aims and hypotheses

The **
*main specific aim*
** of this study is to determine the effect of an intervention designed to increase the use of evidence-based practices included in the ANC package by midwives (and other health professionals) in prenatal clinics in Mozambique. Specifically, we will assess the effect of the intervention on practices related to the detection, treatment and prevention of major health-related conditions (e.g., anaemia, and infectious diseases such as HIV/AIDS, malaria, and congenital syphilis).

Our **
*primary hypothesis*
** is that the intervention will increase the use of such practices in comparison to the standard dissemination channels currently used in the country. A secondary hypothesis is that the intervention will improve the attitudes and readiness of midwives (and other health professionals) to provide all recommended practices during ANC visits to their women clients.

We set out to assess if a multifaceted intervention with several interacting components to increase the use of evidence-based practices in an ANC package would be effective in improving the quality of care of maternal and child health services in Mozambique [19].

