## Methods

This will be a facility-based cluster randomized controlled trial with a stepped wedge design. Figure 1 summarizes the study design. The intervention will be rolled out sequentially to ten ANC clinics in three regions of Mozambique starting a new facility every two months. After two months of baseline data collection in all facilities (months 1 and 2), facility 1 will start at month 3, facility 2 will start at month 5, etc. The order in which the clinics receive the intervention will be determined at random and, by the end of study, all clinics will have received the intervention. Outcomes will be computed at each time point when a new clinic starts the intervention.

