### Study population

#### **
*Participating clusters and women*
**

This study will be conducted in 10 ANC clinics in the three regions of Mozambique. The Ministry of Health pre-selected the 10 clinics according to their programmatic activities and priorities. The pre-selected clinics are shown in Table 1 and Figure 2. They account for a significant proportion of the annual ANC visits in the country.

**Table 1 T1:** Pre-selected ANC clinics

**Region**	**Health Center (HC)**	**Women attending 1**^ **st ** ^**ANC in 2011**

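### The two-round attitude survey gives the secondary hypothesis an effectively uncontrolled before-after comparison, and its baseline window allows one of ten clinics to be surveyed after training

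*Protocol article*

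**What the plan says.** All references are to the protocol article.

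- **Hypothesis** (Study aims and hypotheses): "A secondary hypothesis is that the intervention will improve the attitudes and readiness of midwives" and other health professionals. The matching outcome, the frequency of positive attitudes and readiness, is the last item under Secondary outcomes.
- **Survey timing** (Data collection and management, source of data for secondary outcomes): the questionnaire is given in all participating centres at two points, "one within the first four months of the study period and the second within the last two months of the study period".
- **Comparison** (same section): the first-round answers "will be used as baseline data and will be compared to results from the same questionnaire administered after the intervention".
- **Roll-out** (Methods): "After two months of baseline data collection in all facilities (months 1 and 2), facility 1 will start at month 3, facility 2 will start" in month 5, and so on, "starting a new facility every two months". The Methods also state that "by the end of study, all clinics will have received the intervention".
- **Training** (The intervention, Component 4): all MCH nurses at a site receive a 3-day course when the intervention starts there.
- **Analysis** (Statistical analysis): a generalised linear mixed model using both between-clinic and within-clinic information.

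**The concern.** A stepped wedge separates an intervention effect from a time trend because, at most measurement points, some clinics are exposed and others are not. The attitude survey is taken near the two ends of the schedule, where that contrast is absent or nearly absent.

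Attitudes may change over some 20 months for reasons unrelated to the kits and training. Clinics awaiting the intervention continue standard in-service training, staff change, and taking part in research may itself alter views. A first-versus-second comparison credits all of this to the intervention.

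A smaller issue is that the baseline window runs past the first clinic's start. If staff there are surveyed after their course, and the course improves attitudes, that clinic's measured change is diluted.

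**Working it through.** **Inputs.** Ten clinics (Study population); two baseline months, first start in month 3, one new clinic every two months (Methods); deployment of 22 months (Duration of the project); survey windows as quoted. The study period is read as the 22-month schedule.

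**Step 1: reproduce the calendar.** Facility k starts in month 3 + 2(k − 1) = 2k + 1, which gives months 3, 5, 7, 9, 11, 13, 15, 17, 19 and 21. Total length is 2 + 10 × 2 = 22 months, matching the stated figure.

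**Step 2: count exposed clinics in each survey window,** treating a clinic as exposed from its start month.

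| Months | Exposed | Unexposed |
|---|---|---|
| 1-2 (round 1, first half of window) | 0 | 10 |
| 3-4 (round 1, second half of window) | 1 | 9 |
| 21-22 (round 2) | 10 | 0 |

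**Step 3: can the effect be separated from time?** Take a model with 10 clinic terms, 1 survey-round term and 1 exposure term, 12 columns in all.

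- *Round 1 in months 1-2.* Exposure equals survey round in every clinic. The design has rank 11 of 12, so the effect is not estimable once time is in the model. Replacing the clinic terms by random effects does not help: the intercept, round and exposure columns have rank 2 of 3.
- *Round 1 in months 3-4.* The rank is 12 of 12, but only facility 1 differs from the rest. Exposure changes by 0 in facility 1 and by 1 in the other nine (mean 0.9). The sum of squares is 0.9² + 9 × 0.1² = 0.90. A within-clinic difference has variance 2 per unit cell variance, so the effect has variance 2 / 0.90 = 2.22.
- *Reference: all 11 two-month periods measured.* The design has full rank (21 of 21). Summing exposure squared and removing clinic and period means gives 55 − 385/11 − 385/10 + 55²/110 = 9, so the variance is 1/9 = 0.111. The ratio is 2.22 / 0.111 = 20.

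These variances assume clinic fixed effects and equal cells.

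**Step 4: what the raw before-after difference contains.** With equal clinic weights and an immediate full effect (assumptions), it is 100% of the effect plus the whole time trend if round 1 is in months 1-2. It is (9 × 1 + 1 × 0)/10 = 90% of the effect plus the whole time trend if all clinics are surveyed in months 3-4.

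**Step 5: what one intermediate round would add.** With a clean baseline, a month-12 round and the final round, five clinics are exposed at month 12 (starts in months 3 to 11) and five are not. After removing clinic and round means, each clinic contributes 1/36 + 4/36 + 1/36 = 1/6. The variance is 1 / (10/6) = 0.60. If the 12 months run from the first start, to about month 14, the split is 6 to 4. The sum of squares is then 6 × 0.1067 + 4 × 0.24 = 1.60 and the variance 0.625.

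**The case against.** Several counter-arguments have force.

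- **The two problems do not occur together in full.** A clean baseline gives complete aliasing with time and no contamination. A late baseline gives contamination in one clinic, but an effect that is formally identified. This stands, and the two cases are kept apart above.
- **The randomised order is not worthless for this outcome.** A reader might infer that it contributes nothing. At round 2, exposure ranges from at most about 2 months in facility 10 to about 18-20 months in facility 1, in random order, so a randomised comparison by duration is possible. It does not address exposed versus unexposed, and the article plans no such analysis.
- **The contamination is small and conditional.** Four months is an outer limit, calling the round baseline suggests that a pre-intervention survey is intended, and the study period is not defined (Duration of the project also gives 61 months including formative research). This stands: the ceiling is one clinic in ten. The month numbering in the Methods favours the 22-month reading. On either reading the final two months come after every clinic has started.
- **The comparison is openly described.** The secondary hypothesis, unlike the primary one, names no comparator. That makes this a weak design rather than a contradiction. An analysis plan could add caveats, but it could not create a concurrent control from these two rounds.
- **The intermediate round is not free.** The article does not say who runs the exit survey planned at 12 months, or that the questionnaire's data collector would be present. This stands, so that round is offered only as an option.

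**Conclusion.** The concern holds for the attitude outcome. As scheduled, the comparison is effectively an uncontrolled before-after one. With a clean baseline the effect cannot be separated from calendar time; with a baseline in months 3-4 it rests on one clinic, at 20 times the variance of the full wedge. The mixed model does not repair this.

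The post-training baseline is the lesser part. It affects at most one clinic of ten, only if that clinic is surveyed after its course, and it biases that clinic's change towards zero only if training improves attitudes. The documents do not support reading the whole baseline as compromised.

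The conclusion assumes the 22-month reading and clinics starting on schedule. It concerns one secondary outcome; the primary outcomes come from the registration book and are not touched.

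**What to change.** 1. Require the first questionnaire to be completed at every clinic before that clinic's training, which for facility 1 means by the end of month 2. This changes the timing rule and needs no extra data collection, although facility 1 must be reached earlier than the present window requires.
2. State that the two-round result is an uncontrolled before-after comparison that cannot separate the intervention from time trends, and word the secondary hypothesis and its reporting to match. This costs a sentence or two.
3. Optional: repeat the questionnaire in all ten clinics at about month 12, when roughly half are exposed (5 versus 5, or 6 versus 4 if counted from the first start), and fit survey round and exposure together. The cost is modest: one more round of paper forms and consent. The effect then becomes estimable. Whether the precision is useful depends on the number of providers per clinic, which the article does not give and which should be checked first.
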